#### 2.3.3. Healthy Plant-Based Snacks

The healthy and sustainable plant-based snacks will be developed and produced during Phase 1 of this study by three food companies located in Spain (DELAFRUIT S.L.U., Tarragona), Morocco (ECOMAB SARL, Casablanca), and Turkey (KOCAHAN SEKERLEME, Bursa) and will be consumed during the 3-month intervention by children aged 3 to 11 years.

The composition of the new food products will be based on local and traditional vegetables, fruits, legumes, seeds, and nuts as main ingredients, which are rich in health-promoting bioactive compounds. Processing and preservation strategies will be adapted to retain the nutritional value of the ingredients, and an eco-design methodology will be followed to produce the snacks [40]. In addition, the selection of the ingredients will be carried out beforehand in the three study countries through participatory focus groups involving parents and children. The locally produced plant-based ingredients will be presented to the families to determine their level of knowledge of them and the degree of incorporation in their diets (Table 2). The results of the focus group will allow the food manufacturers to reach a better understanding of the fruits, nuts, and vegetables the children usually consume in each country. Finally, after the preindustrial scale-up, four different snack prototypes to be used during the intervention in each country will be chosen according to the family’s preferences, and the portions and frequency of consumption will be defined to complement the children’s mid-morning and mid-afternoon snack, considering their nutritional and energy needs.

Since the snacks are produced with healthy and Mediterranean ingredients free of toxic agents and contaminants, no problems relating to children’s safety are expected during the intervention study. At the time of family selection, the children’s allergy history will be checked and the organoleptic characteristics of the snack products will be described to parents to verify the children’s acceptance.

The snack products will be produced in a single batch in each country. Once produced, the manufacturers of each country will send them to the corresponding enrolment center prior to the start of the intervention study. The products will be delivered in a lot to the families in the same country at the beginning of the intervention.

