To evaluate the overall effect of the intervention as well as the individual and combining effect of each intervention component, a full-factorial design will be used [34]. This design will allow us to evaluate the independent effect of the different intervention components versus the control group and, simultaneously, the summatory effect of combining different components on increasing the family adherence to the MD. This will therefore provide a stronger inference about the effect on the different implemented interventions [35].

The overall study duration will be 13 months for each participating family, including 3 main visits (V0, V1, and V2) (Figure 2). A prior preassessment visit will be performed at baseline, followed by the intervention study that will be deployed in the last 3 months (between month 10 and 13). According to this timeframe, this study will be arranged in two different phases (Figure 2).

*Phase 1* (*month 0 to month 9*): preassessment. The families will be recruited and included in this study; they will be randomly assigned to the different study groups; and consumption patterns and sociodemographic, socioeconomic, and environmental indicators will be evaluated through specific questionnaires. In addition, the different educational materials and activities, AI-based app, and healthy plant-based snacks will be developed prior to the start of the intervention study. This information will help us understand the context of each participant group and inform our analysis.

*Phase 2* (*month 10 to month 13*): the intervention study will be deployed at the family level. Families will receive the educational materials and activities, the AI-based app, and the plant-based snacks developed in Phase 1, depending on their assigned intervention group. In addition, anthropometrics, lifestyle, dietary, and socioeconomic and environmental indicators will be evaluated through specific questionnaires.

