### 2.2. Family Recruitment and Eligibility

The Spanish families will be recruited by researchers from the Nutrition and Health Unit (Eurecat, Reus) and the Center for Research in Agri-Food Economics and Development (CREDA, Barcelona), and the Turkish and Moroccan families will be recruited by researchers from the Bursa Uludag University and the Unité de Nutrition et al.imentation CNESTEN, respectively. In addition, all countries will have the support of schools, high schools, family associations, and other collaborators such as primary care centers and community centers.

Families will be eligible to participate if they meet the following criteria: (a) families from any socioeconomic status with at least one child younger than 12 years and one adolescent older than or equal to 12 years (overall age range 3–17 years) and that live together; (b) informed consent has been signed by parents and the adolescent; and (c) families have a mobile phone, tablet, or computer with internet access. This inclusion criterion of composition of families and ages of children was selected to capture a range of developmental stages within families, as younger children and adolescents may respond differently to dietary interventions than adults. While this may introduce differences in family structure, it also promotes interaction across ages, potentially enhancing the adoption of healthy eating habits through sibling influence and parental support.

Exclusion criteria will be as follows: (a) having allergies or food intolerances to any of the following plant-based snack ingredients: fruit, vegetables, legumes, cereals, seeds, nuts, and yogurt (only for children under 12 years); (b) disliking any of the snack products (only for children under 12 years); (c) MD Adherence Score (MEDAS) or KIDMED score greater than or equal to 11 points, which is a food pattern already highly concordant with the MD [36]; (d) following a vegan diet (any of the family members); (e) following a prescribed long-term and strict diet for any reason, including diets for weight loss and diets for chronic metabolic or autoimmune disorders such as type 1 diabetes, celiac disease, inflammatory bowel disease, or rheumatoid arthritis (any of the family members); (f) participating in or having participated in a clinical trial or nutritional intervention study in the last 30 days prior to inclusion in this study; (g) no or limited access to the internet; and (h) being unable to follow the study guidelines.

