### 2.3. Interventions

The interventions will involve a combination of digital-based tools and hands-on educational materials and activities, with healthy plant-based snacks developed during Phase 1 of this study. At the beginning of Phase 2 (month 10), there will be prior training for all families, where they will be informed about the specific intervention to which they will be randomly assigned.

The intervention materials and products will be adapted to reflect the cultural preferences and dietary habits of each country. This approach ensures that the interventions are relevant and engaging for families in each country. However, we will maintain some common elements across all interventions to facilitate meaningful comparisons in the study’s outcomes.

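### Snack dislike is screened at V0 on products not yet finalised, so refusal can surface after randomisation in the four snack groups only, where the withdrawal, replacement and per-protocol rules can remove those families one-sidedly

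*Protocol article*

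**What the plan says.** **The criterion.** Section 2.2 excludes families for "disliking any of the snack products (only for children under 12 years"). The criterion applies to every family, whatever group it later joins.

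**How and when it is checked.** Section 2.3.3: "At the time of family selection, the children’s allergy history will be checked and the organoleptic characteristics of the snack products will be described". The description is given to the parents, and its purpose is to confirm acceptance by the children. No tasting by the children is mentioned. Section 2.4 places the eligibility assessment at V0, and sections 2.4 and 2.6 place randomisation after V0.

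**When the products exist.** Section 2.1 requires only that the "healthy plant-based snacks will be developed prior to the start of the intervention study". Section 2.3 likewise speaks of an intervention "with healthy plant-based snacks developed during Phase 1 of this study". Section 2.3.3 adds that, after pre-industrial scale-up, "four different snack prototypes to be used during the intervention in each country will be chosen according to the family’s preferences". Families first receive them late: "The products will be delivered in a lot to the families in the same country at the beginning of the intervention".

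**The calendar.** Section 2.1: "The overall study duration will be 13 months for each participating family", including V0, V1 and V2, "followed by the intervention study that will be deployed in the last 3 months (between month 10 and 13").

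**What happens to a family that cannot take the snacks.** Section 2.8, criterion (1), withdraws a family when a circumstance prevents it from performing study procedures, and it names intake of the study products as an example. Withdrawn participants are replaced by the next eligible one. Section 2.10.1 plans an ITT analysis that includes data from drop-outs, and a per-protocol (PP) analysis limited to families that followed the protocol instructions exactly.

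**The concern.** A dislike criterion keeps the groups comparable if it is applied to all eight groups before allocation and against the product that will be eaten. Here it is applied at the right moment, but to a product that is not yet fixed. Some children will pass at V0 and refuse the real snack at month 10.

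Only families given snacks can show that refusal. Equally reluctant children in the other four groups are never put to the test and stay in. If refusers are then withdrawn, replaced or dropped from the PP set, the snack groups become a selected subset while the comparison groups do not. If families who reject plant-based snacks also improve less in Mediterranean diet adherence, the snack effect is overstated. Replacement restores the head count but not the comparability. The snack contrast is one of the three factors that the full-factorial design exists to estimate.

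**Working it through.** **1. Order of events, set side by side**

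| Step | When | Section |
|---|---|---|
| Eligibility, including (b), by description to parents | V0 | 2.2, 2.3.3, 2.4 |
| Randomisation | after V0, Phase 1 | 2.1, 2.4, 2.6 |
| Snacks developed and produced | Phase 1 (months 0 to 9) | 2.1, 2.3.3 |
| Four products per country chosen | after pre-industrial scale-up | 2.3.3 |
| Snacks reach families | start of intervention, month 10 | 2.1, 2.3.3 |

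Each family's 13 months include V0 and end with the 3-month intervention, so V0 falls at about month 0. Section 2.3.2 supports early allocation: adolescents already assigned to the educational groups help design materials during Phase 1. The order within Phase 1 is otherwise inferred.

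**2. The plan's own sample size**

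Inputs from section 2.7: difference 1 MEDAS point, SD 1.19, alpha 0.05, power 0.80, drop-out 25%.

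- n = 2 × 1.19² × (z₁₋α/₂ + z₀.₈₀)² / 1². With alpha = 0.05/28 (all 28 pairs of eight groups) this gives 44.5, so 45 per group. The article does not state this adjustment, but it reproduces the figure.
- 45 / (1 − 0.25) = 60 per group; 60 × 8 = 480.
- Four of the eight groups include snacks: 4 × 60 = 240 families. The planned drop-out allowance among them is 0.25 × 240 = 60.

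**3. Size of a one-sided removal**

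Let r be the share of snack families removed for refusal, and δ the difference in mean score change between retained and removed families. The full-group mean is (1 − r) × retained + r × removed, so the retained mean exceeds it by r × δ. The documents give neither value; both are assumptions.

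| r | Families of 240 | Bias, δ = 0.5 | Bias, δ = 1 |
|---|---|---|---|
| 5% | 12 | 0.025 | 0.05 |
| 10% | 24 | 0.05 | 0.10 |
| 20% | 48 | 0.10 | 0.20 |

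At r = 10% and δ = 0.5, the bias is 0.05 / 1.19 = 0.04 SD.

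**4. Lost numbers are the lesser issue**

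With 10% extra loss and no replacement, a snack group falls from 45 to 40.5 evaluable families. Power against a control group of 45 at alpha 0.05/28 goes from 0.81 to 0.78 (normal approximation).

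**5. Cost of keeping refusers in the analysis**

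If a share r gains nothing from the snack, a 1-point effect becomes 1 × (1 − r). Power by two-sample t test, SD 1.19:

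| r | Effect | 45 v 45, alpha 0.05 | 45 v 45, alpha 0.05/7 |
|---|---|---|---|
| 0 | 1.00 | 0.976 | 0.888 |
| 10% | 0.90 | 0.944 | 0.795 |
| 20% | 0.80 | 0.884 | 0.668 |

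At alpha 0.05/28, by the normal approximation of step 2, the standard error is 1.19 × √(2/45) = 0.251. At r = 10%, 0.90/0.251 − 3.124 = 0.46, a power of 0.68 against 0.81 undiluted. The factorial main effect of snacks (4 × 45 = 180 v 180, alpha 0.05) stays above 0.999 at every r shown.

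**The case against.** **No rule re-applies exclusion (b) after allocation.** A reader might infer that (b) itself acts after randomisation and on one side. The documents do not say so: eligibility is assessed once, at V0, for all families. What stands is that the V0 screen is imprecise. Any one-sided loss comes from section 2.8 and the PP definition, which would also remove refusers who had passed a perfect screen.

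**Dislike is not named as a reason for withdrawal.** Criterion (1) speaks of a circumstance that prevents compliance, and with four products a child who dislikes one can eat the others. This is fair. But product intake is named in the criterion, so refusal of the snacks as a whole can be read into it, and sites may read it differently.

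**ITT is planned.** Section 2.10.1 includes drop-outs' data, and the handling of missing V2 scores may lie in an analysis plan not shown. The concern about ITT is therefore conditional on withdrawn families having no V2 score. The PP set has no such condition.

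**Dislike will be limited.** Focus groups with parents and children, and preference-based choice of products, should reduce refusal. They do not screen each enrolled child.

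**Much larger figures are tempting.** With 10% disliking each of four products independently, 1 − 0.9⁴ = 34% would dislike at least one. Reading that as 34% lost requires independent dislikes and every such family leaving; nothing supports either. Nor is the 1-point target a sound yardstick: it is a MEDAS difference, measured in parents, while children aged 3 to 11 eat the snacks and are scored on KIDMED.

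**Allergy.** The V0 check is about 10 months old at delivery, but a medical history is taken at V1, families report adverse events throughout, and suspected reactions go to the study doctor. Any further detail may be in the full protocol, so no defect is claimed here.

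**Conclusion.** The point holds in a limited form. Exclusion (b) is screened at V0 against products that are not final, so it cannot reliably remove non-accepting children before randomisation. Refusal of the real product can appear only in the four snack groups, and sections 2.8 and 2.10.1 as worded can remove those families from that side alone.

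The bias is of unknown size and probably small: about 0.05 points at 10% removed and a 0.5-point difference in score change. It rests on an assumed refusal rate, an assumed difference in response, and on sites treating refusal as grounds for withdrawal. The timing rests on the stated 13 months per family; the timeline figure was not available. The change is worth making because it is cheap and protects a randomised contrast that is central to the design.

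**What to change.** 1. **Sections 2.2 and 2.3.3.** Define (b) as willingness of the child to eat the listed ingredient classes and planned snack formats. Ask it of every family at V0, and state that it is not re-applied after allocation.
2. **Section 2.8.** State that a family whose child refuses or must stop the snacks discontinues the snacks only, is neither withdrawn nor replaced, attends V2, and is analysed in its randomised group under the planned ITT.

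**Cost.** Wording in three sections, and V2 for families that would otherwise have left. The statistical price is dilution: with 10% non-takers a 1-point effect becomes 0.90. The snack main effect hardly notices. A single snack group against control loses a few points of power at alpha 0.05 (0.976 to 0.944) and more under strict multiplicity adjustment (0.888 to 0.795 at 0.05/7; about 0.81 to 0.68 at 0.05/28). That diluted estimate is the effect of offering the snacks, and it keeps the comparison randomised.

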### 2.4. Visits and Procedures

All families will attend the school facilities or at research centers where they are recruited on 3 different occasions (V0, V1, and V2). The visits will be divided between the two study phases previously described. Figure 4 shows the schedule of each visit, which will follow the same timeline for each enrollment center.

In Phase 1, families will be recruited and a preassessment visit will be carried out (V0). At this point, families will be assessed against the eligibility criteria and then informed about this study in a group session. The informed consent document will be signed by parents and adolescents. The researchers will then instruct them on the completion of online questionnaires at home through the Microsoft Forms web-based application to assess socioeconomic, sociodemographic, lifestyle, and environmental indicators. This information will be valuable in predicting selected behavior sub-domains that will be evaluated based on a theoretical model derived from the COM-B model for behavior change. A theoretical model based on information on physical activity, food habits, lifestyle, and social behavior will be created, aiming to achieve the best outcomes via surveys that are not too long [41]. In addition, families will complete a 7-day semi-weighted food record (7DWR) to assess dietary habits and consumption patterns at baseline. After V0, the selected families will be randomly allocated to the different intervention/control groups.

In Phase 2, the selected families will attend V1 and V2 at the beginning and end of the 3-month intervention study, respectively. In V1, families will receive group training according to the different intervention groups: on the use of the S2H app, on snack consumption, and/or on the use of educational materials and activities. In addition, each family will be visited individually by expert nutritionists who will assess adherence to the MD through the MEDAS and KIDMED questionnaires for adults and children, respectively, and will take anthropometric measurements (body weight, height, BMI, waist circumference, blood pressure, and heart rate) for each family member. Nutritionists will also complete a medical history, including the use of medications and/or supplements. At the end of V1, time will be left for families to self-complete online questionnaires through the Microsoft Forms web-based application. The questionnaires will be adapted according to the age of the family members to assess socioeconomic, lifestyle, dietary, and environmental indicators. In addition, families will complete a 7DWR and report food expenses during the week after V1.

During the 3-month intervention, families will use the different educational components and products. They will be in continuous contact with the research team to ensure compliance and report any adverse events, particularly in children assigned to consume the snack products. In V2, each family will be visited individually, the same parameters as those in V1 will be measured by nutritionists, and data on socioeconomic, lifestyle, dietary, and environmental indicators will be self-reported by each family member by means of online questionnaires. A closing session of this study will be carried out by researchers once the intervention is completed to inform the families of the main results of the study.

### 2.5. Outcomes

The primary outcome will be adherence to the MD measured through the MEDAS and the KIDMED questionnaire score in parents and children, respectively. The MEDAS is an extension of a 9-point score developed in the Prevención con Dieta Mediterranea (PREDIMED) trial [42,43]. It consists of 2 questions about eating habits, 8 questions about the frequency of consumption of typical foods of the MD, and 4 questions about the consumption of foods not recommended in this diet. Each question is scored with 0 (noncompliant) or 1 (compliant), and the total score ranges from 0 to 14, so a score of 14 points means maximum adherence. The KIDMED score consists of 16 items with affirmative or negative answers, where there are 4 questions denoting a negative connotation to the MD and 12 questions denoting a positive connotation. A positive answer to questions denoting negative connotation is scored with −1, while positive connotation questions are scored with +1. The total score ranges from 0 to 12, so a score of 12 points indicates good adherence [44]. To avoid deviations in outcomes (such as physical activity or portions of food), surveys will be assessed by researchers during visits.

The secondary outcomes will include the following:Anthropometric data: body weight, measured in all family members with a Tanita DC 430S-MA (Tanita Corp., Barcelona, Spain); height, obtained using a wall-mounted stadiometer (Tanita Leicester Portable; Tanita Corp., Barcelona, Spain); waist circumference, measured at the level of the narrowest region between the last costal (10th rib) and the edge of the iliac crest using a 200 cm anthropometric steel measuring tape; and BMI, obtained using the formula of weight in kilograms divided by the square of the height in meters.Systolic and diastolic blood pressure and resting heart rate, measured twice at 1 min intervals using an automatic sphygmomanometer (OMRON HEM-907; Peroxfarma, Barcelona, Spain).Sociodemographic and socioeconomic factors, measured in parents and adolescents via an adapted questionnaire from Rodríguez-Rodríguez et al. [45]. This questionnaire will collect information regarding age, gender, household members, marital status, income, level of education, and employment status.Social factors, measured in all family members via an adapted questionnaire from McIntosh et al. [46]. This questionnaire will collect information regarding work flexibility and satisfaction, work–life balance, lifestyle, time spent with children, family decision making, and task responsibility.Physical activity, measured in all family members by validated physical activity questionnaires, IPAQ for adults [47] and PAQ-C [48] and PAQ-A [49] for children aged over 8 years and adolescents, respectively.Health factors, measured in all family members via the General Health Questionnaire (GHQ) [50]. This questionnaire will ask about different aspects related to health and healthy lifestyle such as sleeping habits, hospitalization, and prescribed medications.Mediterranean lifestyle habits, measured only in parents via the Mediterranean Lifestyle index (MEDLIFE), which will capture adherence to an overall Mediterranean healthy lifestyle [51].Diet quality, measured via the Healthy Diet Index (HDI) [52] for adults and KIDMED [44] for adolescents and children.Quality of life, measured via the EQ-5D-5L scale for adults [53] and the KIDSCREEN scale for adolescents and children aged over 8 years [54]. The EQ-5D-5L assesses five dimensions: mobility, self-care, usual activities, pain/discomfort, and anxiety/depression. The KIDSCREEN assesses children’s and adolescents’ subjective health and well-being.Nutritional knowledge, measured via a short consumer-oriented nutrition knowledge questionnaire for adults [55] and the HELENA questionnaire for adolescents, which also includes a self-reported food frequency questionnaire [56]. These questionnaires will measure the parents’ and adolescents’ knowledge of a healthy diet.Attitudes and beliefs in relation to food, measured via an adaptation of the McIntosh et al. questionnaire [46] and the Early Parenting Attitudes Questionnaire (EPAQ) [57]. These questionnaires will assess the family eating habits and attitudes of and barriers faced by parents and adolescents in relation to the MD.Family weekly food intake, measured in all family members via a 7DWR, which involves an individual weighing of each food item prior to consumption. The 7DWR will be completed during the week after visit V0 and V1 and the week prior to visit V2. In V0, families will receive instructions for the correct completion. Nutritionists will instruct families on the use of kitchen scales. Apart from food, 7DWR will allow data on the average intake of macro- and micronutrients to be obtained.Family weekly food expenses, measured per family unit using shopping receipts collected during the week after visit V0 and V1 and in the week prior to visit V2. In each visit, families will be provided with an envelope for collecting the shopping receipts and other food expenses for a week.Environmental impact of food consumption, assessed by converting the 7DWR consumption quantities into kg of CO_2_ emission, land use, and water footprint using existing data in the literature on the environmental impacts of different food groups [58,59,60].Economic impact, estimated using the data obtained from family weekly food records and expenses reported by means of shopping receipts. Two measurements will be carried out at the beginning and end of the 3-month intervention, and potential effects of promotions at the specific retail outlet as well as family events and the seasonal effect will be controlled.

Each specific outcome and visit are summarized in Figure 4.

The integrated data from the primary and secondary outcomes, including MD adherence, diet quality, family weekly food intake, and food expenses, will provide an overview of the three main impact dimensions: quality of diet and health, economic, and environmental. These indicators will allow us to better understand the reasons behind dietary behavioral changes to facilitate the scaling-up of the most effective interventions or to redesign the less effective ones in the future.

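### The V1 food record and shopping receipts are kept in the first week of the intervention, so economic impact and any V2-versus-V1 change in intake, spending or footprint start from an exposed week

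*Protocol article*

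**What the plan says.** Section 2.4 (Visits and Procedures) places V1 at the start of the treatment period: "the selected families will attend V1 and V2 at the beginning and end of the 3-month intervention study, respectively". What happens at V1 is specific to the arm: "In V1, families will receive group training according to the different intervention groups", covering the app, the snacks and the educational materials. The food record and spending data come afterwards: "families will complete a 7DWR and report food expenses during the week after V1". Section 2.5 (Outcomes) gives the same timing for the record ("The 7DWR will be completed during the week after visit V0 and V1 and the week prior to visit V2") and for household spending ("measured per family unit using shopping receipts collected during the week after visit V0 and V1 and in the week prior to visit V2").

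On the snacks, section 2.3.3 states: "The products will be delivered in a lot to the families in the same country at the beginning of the intervention".

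Section 2.5 defines economic impact from the food records and receipts, with two measurements, one at each end of the 3-month intervention. It derives environmental impact from the 7-day food record (7DWR) without naming a reference visit.

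There is also an earlier record. In Phase 1, at V0, "families will complete a 7-day semi-weighted food record (7DWR) to assess dietary habits and consumption patterns at baseline". Receipts are collected after V0 as well.

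**The concern.** A change score needs a starting value that the treatment has not touched. The measurements labelled V1 do not all meet that condition. MEDAS, KIDMED and anthropometry are taken at the V1 visit itself. The food record and receipts carry the same visit label but are collected over the following seven days, after training and with the intervention under way. The closing record is placed before V2, so the two ends of the interval are not handled alike.

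Several secondary outcomes rest on these weeks: food intake, food expenses, economic impact, and the CO2, land and water footprints. If families change what they buy and eat as soon as they receive meal plans, materials or snacks, part of the effect is already in the starting value and is subtracted out. Economic impact is the most exposed, because its definition names only the beginning and end of the intervention.

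**Working it through.** The plan gives no standard deviation, target difference or sample size for intake, spending or footprint. Its 45 families per group (60 after drop-out) are for the MEDAS score, and this point does not depend on them. The check is therefore one of timing, followed by simple algebra.

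**Timing, from sections 2.1, 2.3.3, 2.4 and 2.5**

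| Week | Position | Exposure |
|---|---|---|
| After V0 | Phase 1 (months 0 to 9), before randomization | No component deployed |
| After V1 | First week of Phase 2 (from month 10) | Arm-specific training given; snacks delivered at the start |
| Before V2 | Last week of Phase 2 (to month 13) | Full intervention period |

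The two economic-impact measurements map to the second and third rows. V0 can precede the intervention by about 10 months, so it cannot be the measurement at the beginning of the intervention.

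**What each contrast estimates.** Let E be the difference between an intervention arm and control in the final week, and let f be the share of E already present in the week after V1. In expectation, under randomization:

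- V2 minus V1, between arms: E − fE = (1 − f)E.
- V2 minus V0, between arms: E − 0 = E.
- Final week alone, between arms: E.

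Only the first is distorted. The documents give no value for f, so the following values are assumptions that show the range:

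| Assumed f | Share of E kept by V2 minus V1 |
|---|---|
| 0 | 1 − 0 = 100% |
| 0.25 | 1 − 0.25 = 75% |
| 0.50 | 1 − 0.50 = 50% |
| 0.75 | 1 − 0.75 = 25% |

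f probably differs by component. Snacks are delivered at the start and are meant to be eaten throughout the three months, so f could be high for their contribution to intake. The educational programme runs at four activities a month (12 in all), so about one would be done by the end of week 1 and f could be low. The Discussion foresees declining use, particularly of the app. If week 1 were the peak, f would exceed 1 and the V2-versus-V1 change would have the wrong sign.

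**Receipts and study snacks.** Assume the snacks are supplied free. In the 2 × 2 × 2 design, 4 of the 8 groups receive them. Let s be the weekly value of study snacks eaten but absent from receipts.

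- V2 minus V1: both weeks omit s, so the omission is s − s = 0 if consumption is similar.
- V2 minus V0: only the later week omits it, so recorded spending falls short by s relative to food eaten.
- Final week, snack arms against the others: also short by s.

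The receipt issue therefore belongs to the contrasts that avoid the timing problem. It does not add to the V2-versus-V1 distortion.

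**The case against.** The strongest reply is that the trial does have an untreated reference. The protocol attaches the word baseline to the V0 record, made before randomization, and V0 receipts exist too. Section 2.10.1 lists V2 versus V0 beside V2 versus V1, although that sentence follows the one on MEDAS and KIDMED scores. No reference visit is fixed for intake, expenses or footprint, so an analyst could use V0 throughout. This stands. A reader might infer that the trial's baseline diet data as a whole are contaminated, and the documents do not support that.

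Season is a weak argument against V0. If V0 falls at month 0, the V0 and pre-V2 weeks are about 13 months apart and so nearly in the same season, whereas V1 to V2 spans three months. Visits follow the same timeline in each centre and arms are randomized, so season is largely shared between arms. Section 2.5 also says seasonal effects on economic impact will be controlled. What remains against V0 is its distance: up to about 10 months before the intervention, with a weaker link to later values likely, and with some adolescents in the education arms taking part in cocreation sessions in between.

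It can also be said that only secondary outcomes are involved, that the values of f are assumed, and that snack pricing is analysis-plan detail. The first two are right and limit the point. The third is why snack pricing is only a secondary suggestion here. The visit schedule in Figure 4 is not shown, but the text gives the week after V1 in both section 2.4 and section 2.5.

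None of this rescues economic impact, whose two measurements bracket the intervention and so begin in week 1.

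**Conclusion.** The point holds for a defined set of secondary results: economic impact as specified, and any V2-versus-V1 change in food intake, food expenses or 7DWR-based footprint. These start from a week in which the intervention is already running, and they understate the effect to the extent that behaviour has changed by then. The loss is a fraction f of the effect. The documents do not allow f to be estimated, so the percentages above illustrate the mechanism and are not a finding about this trial.

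The conclusion assumes that families begin using their components once trained and supplied. Nothing in the article says that use is held back until the record week is over.

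Two stronger readings should be set aside. The primary outcome and its sample size are not touched, because MEDAS and KIDMED are assessed at the V1 visit. And missing snack receipts do not compound the V1-to-V2 problem, because the omission largely cancels in that contrast.

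**What to change.** Move the V1 food-record and receipt week to the week before V1, ahead of training and snack delivery, so that it mirrors the week before V2. No visit is added. Families are first taught the food record at V0, but that may be many months earlier and envelopes are currently handed out at visits. The cost is sending the notebook and envelope ahead of V1 with a reminder of the weighing instructions.

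If the week cannot be moved, name V0 as the reference for intake, expenses, footprint and economic impact. One way is to compare arms on the pre-V2 week, adjusted for the V0 value. This costs a sentence in the analysis section and an amended definition of economic impact.

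As a secondary measure, if the study snacks are free to families, report receipt spending with and without an imputed price for snacks recorded in the 7DWR, wherever spending is compared with V0 or between arms in the final week. This needs one price per snack product.
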